### Handling Missing Data

Our general approach to missing data will involve taking advantage of all observed information while not exaggerating the precision of findings based on incomplete data [41,42].

All variables described for our final regression models will be used in our imputation procedures. That is, outcome measures (at 3-month and 9-month follow-up analyzed separately), treatment condition, baseline outcome variables, strata variables (sex and number of screening experience factors present), sociodemographic characteristics (age, race, and ethnicity), the time elapsed between baseline and follow-up survey (at 3-month or 9-month follow-up), and school. The treatment and control group participant data will be imputed separately [43].

Multivariate imputation by chained equations [44] methods using PROC MI and MIANALYZE procedures in SAS will be used to create multiple imputations (replacement values) for multivariate missing data (eg, continuous, binary, unordered categorical, and ordered categorical data) based on a fully conditional specification [45], where each incomplete variable is imputed by a separate model [46]. All missingness (nonresponse, program attrition, or study loss to follow-up) will be treated the same way for our benchmark analysis. Additional analyses (see Sensitivity Analysis) will be explored where reasons for program attrition are accounted for in the generation of imputed covariate and outcome values. All variables (ie, outcome and baseline characteristics) described in the above analysis models will be used for the imputation procedures. The number of data sets to be imputed will be determined using the quadratic rule recommended by von Hippel [47]. In addition to the baseline value of the outcome of interest, age, race and ethnicity, the sex assigned at birth, and the number of screening experience factors (1 or 2; ie, adolescents had either exposure to violence or a prior or current experience with a romantic relationship or both), and time (days) between baseline and 3-month or 9-month follow-up will be included in our final analysis models (ie, linear and logistic regression).

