### Follow-up Data Collection

Follow-up surveys were administered at 2 separate time points following the completion of the About Us intervention (approximately 3 months and 9 months postprogram implementation). Similar to baseline data collection for cohort 1 (spring 2018), cohort 2 (fall 2018), and cohort 3 (spring 2019), most follow-up surveys were conducted in-person on school or SBHC grounds. Upon receipt of a signed assent form, adolescents completed the survey on a self-administered tablet device via the Qualtrics Offline Surveys application and in the presence of an EDC. For any adolescents who transferred or were absent, a follow-up contact protocol was used to locate and provide an opportunity to complete the survey. Specifically, using contact data provided by the adolescent at the baseline or 3-month survey, EDCs would undertake a series of contacts through email, text message, cell phone calls, home phone calls, and/or social media messaging, sending the adolescent a unique link to the follow-up survey. Adolescents received a US $10 incentive for each survey completed up to the end of March 2020.

Follow-up surveys for cohorts 4 and 5 were affected by the COVID-19 pandemic due to school closures and travel restrictions preventing evaluation staff from traveling to study sites to administer the surveys. As a result, the study team adopted an online follow-up protocol as the primary approach to administering follow-up surveys and increased the online survey incentive to US $25, as the literature shows this amount is more effective in increasing response rates [29].

Throughout the study and depending on whether the cohort was surveyed during the pandemic, it was possible for participants in both the intervention and control groups to receive incentives totaling as little as US $10 and as much as US $60. Survey incentives offered to all participants were different than program incentives offered only to those in the intervention group who completed About Us program sessions.

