### Statistical Analysis Models

For dichotomous outcomes at 9 months, we will use logistic regression models with covariates (see Textbox 2) for the intervention, baseline outcome variables, strata variables (sex assigned at birth and number of screening experience factors present), sociodemographic characteristics (age and race and ethnicity), the time elapsed between baseline and the follow-up survey (at 3-month and 9-month follow-up), cohort, and school. For continuous outcomes, we will use linear regression models with covariates for the intervention, baseline outcome variables, strata variables (sex and number of screening risk factors present), sociodemographic characteristics (age and race and ethnicity), the time elapsed between baseline and follow-up surveys (at 3-month and 9-month follow-up), cohort, and school. Additional (exploratory) analyses will test for 3-way and 2-way statistical interactions and adjust for prognostic factors such as potential confounders of intervention effects. Similarly, we will include a covariate that captures whether our outcome data were collected pre-COVID-19 versus during the COVID-19 pandemic. Potential 2-way interactions involving this covariate and intervention group, age and grade, and relationship status will be examined to test the differential effects of the pandemic on outcomes of interest.

Covariates included in impact analyses.**Screening factor:** one or two screening factors present (categorical variable).**Age (years):** baseline date to DOB (continuous variable).**Sex:** sex assigned at birth; 1=male, 2=female (dichotomous variable).**Race and ethnicity:** White, Black, Hispanic, other (categorical variable).**Number of days between baseline and the follow-up survey (3 or 9 months):** follow-up date to baseline date (continuous variable).**Cohort:** cohort 1 (spring 2018), cohort 2 (fall 2018), cohort 3 (spring 2019), cohort 4 (fall 2019), and cohort 5 (spring 2020; categorical variable).**School:** high schools 1 to 7.

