### Sensitivity Analysis

In addition to the benchmark analyses described above (3-month and 9-month follow-up examined separately), two types of analyses (ie, complete case analysis—no imputation for missing data—and modified ITT with imputed data) will be implemented using procedures similar to the benchmark analyses (linear and logistic regression models). The robustness of the inferential findings will be assessed by comparing differences in analytical findings across the three types of analyses (ITT with imputed data, complete case analysis, and modified ITT).

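### The imputation list omits cohort, contradicting its own rule, and on its natural reading imputes the 9-month primary outcome without the 3-month outcome; the benchmark odds ratio could shift either way if loss differs by arm

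*Protocol article*

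**What the plan says.** All places are in the Methods of the protocol article.

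- **Analysis model.** Under Statistical Analysis Models, the logistic model for 9-month outcomes ends with "the time elapsed between baseline and the follow-up survey (at 3-month and 9-month follow-up), cohort, and school". The linear model has the same terms, and the covariate box lists the cohorts through "cohort 4 (fall 2019), and cohort 5 (spring 2020; categorical variable". The only earlier measurement of the outcome in this model is the baseline one.
- **General rule for imputation.** Handling Missing Data gives it twice: "All variables described for our final regression models will be used in our imputation procedures", and, after the list, "All variables (ie, outcome and baseline characteristics) described in the above analysis models will be used for the imputation procedures".
- **Explicit list.** Between those two sentences comes "That is, outcome measures (at 3-month and 9-month follow-up analyzed separately), treatment condition, baseline outcome variables, strata variables", then sociodemographic terms, then "the time elapsed between baseline and follow-up survey (at 3-month or 9-month follow-up), and school". Of the model terms named in the Statistical Analysis Models text, only cohort is absent.
- **Time points.** Sensitivity Analysis refers to the "benchmark analyses described above (3-month and 9-month follow-up examined separately".
- **Pandemic.** Follow-up Data Collection says "Follow-up surveys for cohorts 4 and 5 were affected by the COVID-19 pandemic due to school closures".

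The benchmark data set contains all randomized participants with missing outcomes imputed (Generalities of Statistical Analysis Methods). Arms are imputed separately.

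**The concern.** The primary result is the imputed one, so the imputation model is part of the primary analysis. Two features of its description matter.

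First, the rule includes cohort and the list that defines the rule does not. A programmer is likely to code the list. Cohort marks the participants whose follow-up was disrupted and moved online, so it may well predict who is missing.

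Second, the rule does not bring in the 3-month outcome, because the 9-month model does not contain it. The wording on separate time points suggests that each follow-up is imputed on its own. A participant who answered at 3 months and was lost by 9 months would then be imputed without their most recent report of the same behaviour. If that report predicts loss differently in the two arms, the treatment effect is distorted.

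The planned sensitivity analyses are weak protection on this second feature. Complete-case analysis also ignores the 3-month outcome. Modified ITT requires at least one follow-up, so anyone in it without a 9-month survey has a 3-month one, yet it is to follow procedures like the benchmark's. Only the exploratory mixed model uses all time points.

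**Working it through.** **Yardstick from the plan.** Power Analyses gives a 9-point difference, prevalence ratio 0.74 and OR 0.65. Control prevalence = 0.09 / (1 - 0.74) = 34.6%; intervention = 34.6% - 9 points = 25.6%; OR = (0.256/0.744) / (0.346/0.654) = 0.65, which reproduces the plan's figure. ln(0.65) = -0.43. The plan gives no figure for missingness or for the imputation.

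**Inputs from the plan.** 533 randomized (316/217), 3:2 allocation, five cohorts, logistic imputation separately by arm.

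**Assumed inputs.** 27% to 37% of 9-month outcomes missing, more in cohorts 4 and 5; a conditional log-OR of 1.5 between the 3-month and 9-month outcomes; the 3-month outcome fully observed. There were 10 imputations and 400 replicates per scenario. The analysis model had arm, baseline outcome and cohort. The listed imputation model was reduced to baseline outcome within arm; school, elapsed time and the other listed terms were not simulated.

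**Formula.** Shift = mean log-OR under the method minus mean log-OR with full data. Monte Carlo standard errors of the shifts are 0.006 to 0.009.

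| Scenario | Missing, interv./control | OR full data | OR as listed | OR + cohort | OR + cohort + 3-month | Shift as listed | Shift complete case |
|---|---|---|---|---|---|---|---|
| 1. Loss unrelated to 3-month outcome | 27% / 27% | 0.599 | 0.604 | 0.601 | 0.602 | +0.009 | +0.001 |
| 2. Related equally in both arms | 32% / 33% | 0.601 | 0.606 | 0.605 | 0.597 | +0.009 | +0.002 |
| 3. Related in intervention arm only | 34% / 27% | 0.610 | 0.530 | 0.524 | 0.605 | -0.141 | -0.154 |
| 4. Related in control arm only | 27% / 36% | 0.601 | 0.709 | 0.711 | 0.600 | +0.165 | +0.168 |
| 5. Extra intervention-arm loss in cohorts 4-5 | 37% / 27% | 0.598 | 0.647 | 0.617 | 0.616 | +0.078 | +0.009 |
| 6. No direct effect in cohorts 4-5 | 27% / 27% | 0.697 | 0.679 | 0.698 | 0.697 | -0.026 | -0.032 |

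**3-month outcome (scenarios 3 and 4).** The shifts are 0.141/0.43 = 33% and 0.165/0.43 = 38% of the design effect, in opposite directions. With both variables added they fall to -0.008 and -0.001. Complete-case analysis shifts almost identically, so its agreement with the benchmark would reassure falsely.

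**Cohort (scenarios 5 and 6).** In scenario 5 the shift of 0.078 falls to 0.031 when cohort alone is added, so cohort accounts for 0.078 - 0.031 = 0.047. The remainder probably reflects sparse by-arm cohort cells and a small ridge term in the simulation. In scenario 6, adding cohort removes the shift of -0.026. Complete-case analysis would differ visibly from the benchmark in scenario 5, but not in scenario 6.

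**Neither mechanism (scenarios 1 and 2).** The shift is about 0.01, within or close to simulation error.

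**The case against.** The strongest reply is that this is a drafting slip. The section states the inclusive rule on both sides of the list, and that rule covers cohort. The word for separate analysis can describe the outcome models alone, and the section opens with the aim of drawing on everything observed. Randomization was within school-by-semester cohorts and arms are imputed separately, so omitting cohort should matter little unless loss differs by arm or the effect varies by cohort. The documents report neither. Even the larger shifts are 0.141/0.252 = 0.56 and 0.165/0.269 = 0.61 of the simulated standard deviation of the estimate. They also assume a fully observed 3-month outcome.

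Much of this stands, and it rules out several stronger readings that a reader might infer:

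- *Cohort has been dropped.* Not settled; rule and list conflict.
- *The 3-month outcome is expressly excluded.* It is not; exclusion is the natural reading only.
- *Cohort 4 and 5 outcomes would be imputed at an all-cohort average.* They would not; imputation still conditions on arm, baseline outcome, school, elapsed time and the other listed terms.
- *Missing at random necessarily fails.* That depends on mechanisms the documents do not describe.
- *The closing sentence of Handling Missing Data contradicts the model by leaving out cohort and school.* It is worded as an addition and also omits the treatment term, so it is not a full specification.

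What the reply does not answer is that the inclusive rule, even taken at face value, never brings the 3-month outcome into the 9-month imputation.

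**Conclusion.** The point holds as a contradiction over cohort and a poorly fixed choice over the 3-month outcome. It does not establish that the primary result will be biased.

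The larger risk comes from the 3-month outcome: about -0.14 or +0.17 on the log-OR if 9-month loss depends on it in one arm only. Omitting cohort is the smaller risk: about 0.05 to 0.08 if cohort-related loss differs by arm, and about 0.03 if the effect varies by cohort. Both are negligible when loss is unrelated to these variables or balanced across arms.

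These sizes rest on the assumed missingness and correlation and on a reduced imputation model. They apply only to participants who answered at 3 months but not at 9, a number the documents do not give. Arm-specific loss is conceivable, because only the intervention arm had session reminders and a US $30 attendance incentive, but no attrition by arm is reported.

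**What to change.** In Handling Missing Data:

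1. Add cohort to the explicit list, so that list and rule agree.
2. State that the 3-month and 9-month outcomes are imputed jointly within each arm, while the outcome analyses remain separate by time point.
3. Align the closing sentence with the Statistical Analysis Models covariates by naming cohort and school.

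The cost is a few lines of text and code and no new data. The downside is a slightly larger imputation model with some sparse by-arm cohort and school cells. How to stabilise the logistic imputations in those cells, for example by augmented likelihood, is an implementation choice and not part of the required change.

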For this study, the group-based content was delivered by trained facilitators (eg, health educators) from participating SBHCs. The app-based content was housed on a secure website and accessed through tablets with unique logins for each participant. Online activities were completed individually during each session (eg, completing a poll or watching and responding to a brief video). Several lessons also included homework activities that encouraged communication between students and a caring adult. Additional details of About Us are displayed in Table 1.

Participants assigned to the treatment group attended group sessions at the designated space. Health educators followed up with students who missed a session to engage them and remind them of the next session. Participants assigned to the treatment group received a US $30 incentive if they attended 6 or more sessions.

**Table 1 table1:** About Us intervention components.

Component	Amount, duration, and intended dosage	Content	Who delivers	Setting
Group-based sessions	10 (2 prelessons and 8 regular lessons) over 4-9 weeks for a total of 10 hours of programming.	Characteristics of healthy and unhealthy relationships, communication skills (having difficult conversations, such as sexual consent, sexual boundaries, and condoms; using “I” statements); personal and sexual boundaries and sexual consent; condom and contraceptive use; influences on sexual decisions in relationships; ending relationships.	Trained health educators from the school-based health centers.	During school (students pulled out of class to come to the health center or other agreed-upon space on the school campus).
Online work during regular group-based sessions	Approximately 15 minutes in each regular lesson; students are able to revisit content from prior lessons outside of group sessions during the implementation period.	Same as above; online activities allow for the review and application of key concepts and the personalization of content for each lesson.	Trained health educators from the school-based health centers will prompt and support students using the tablets and the application during the group sessions.	Same as above.

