### Generalities of Statistical Analysis Methods

Statistical analysis will be undertaken using SPSS and SAS. All participants randomized to either intervention (About Us) or BAU will be included in the analyses using the intent-to-treat (ITT) principles. Our benchmark analysis data set will include all randomized participants with imputed data for missing covariate and outcome variables.

As part of our sensitivity analyses, two additional types of analyses will be implemented: modified intent-to-treat (modified ITT) and complete case analysis.

Modified ITT analysis (ie, analysis based on a data set that includes all randomized subjects who provide baseline measurements on primary and secondary outcomes and have at least one follow-up assessment) will also be implemented under different conditions for missing data adjustment (described below).

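### The benchmark imputation of the intervention arm ignores attendance, so the ITT effect is biased if survey loss differs between students who attended the programme and those who did not

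*Protocol article*

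**What the plan says.** Under Generalities of Statistical Analysis Methods, the article defines an intent-to-treat benchmark: "Our benchmark analysis data set will include all randomized participants with imputed data for missing covariate and outcome variables".

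Handling Missing Data then sets how the imputation works:

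- All causes of missingness are pooled: "All missingness (nonresponse, program attrition, or study loss to follow-up) will be treated the same way for our benchmark analysis".
- The arms have separate models: "The treatment and control group participant data will be imputed separately".
- The itemised variables are the outcome, treatment condition, baseline outcome, sex, number of screening factors, age, race and ethnicity, elapsed time and school. Attendance is not among them. Nor is cohort, although Statistical Analysis Models makes it a covariate. A later sentence is broader: "All variables (ie, outcome and baseline characteristics) described in the above analysis models will be used for the imputation procedures".
- A further analysis is announced: "Additional analyses (see Sensitivity Analysis) will be explored where reasons for program attrition are accounted for in the generation of imputed covariate and outcome values".

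The Sensitivity Analysis section names "two types of analyses (ie, complete case analysis" without imputation, and modified ITT with imputation. It names no analysis that uses attendance or reasons for programme attrition.

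Attendance was tracked for each participant. Under Intervention, students in the treatment group "received a US $30 incentive if they attended 6 or more sessions", and health educators followed up those who missed a session.

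**The concern.** Programme attrition describes how much treatment a student received. Loss to follow-up describes whether the outcome was observed. A student can have either without the other, and an ITT estimate has to carry the diluted effect in those who were assigned but scarcely exposed.

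Imputing the intervention arm without attendance assumes that, given baseline variables, timing and school, whether an outcome is missing is unrelated to attendance, or that attendance does not affect the outcome. In this trial both parts are open to doubt. The programme is meant to work through its sessions. The article also gives reasons why non-receipt and non-response could coincide:

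- Limitations says that pandemic closures kept some recruited students from receiving the intervention and forced follow-up online.
- Follow-up Data Collection says that surveys of cohorts 4 and 5 were disrupted.
- Limitations also says that some students moved to schools outside the study and were lost. A move of that kind plausibly ends sessions and contact together.

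If non-attenders are under-represented among responders, the imputed values come from a group with more exposure than the arm as a whole. The estimate then moves toward the effect under full attendance while still being labelled ITT.

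**Working it through.** **Figures from the article.** Power Analyses gives a 9-point difference and a prevalence ratio of 0.74. The implied control prevalence is 0.09 / (1 − 0.74) = 34.6%, and the intervention prevalence is 25.6%. The implied odds ratio is 0.65, as stated. A pooled two-proportion formula gives 337 control and 506 intervention participants, close to the stated 339 and 508, and power at 339 and 508 is 80.3%. The sample size is not at issue. These figures only supply the scale.

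**Assumptions, because the article does not give them.** The benefit is 9 points in attenders and none in non-attenders. Let q be the share attending, and rA and rN the survey response in attenders and non-attenders.

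**Formulas.**

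- True ITT effect = 9 × q.
- Attender share among intervention responders: s = q·rA / (q·rA + (1 − q)·rN).
- Large-sample effect when imputing without attendance = 9 × s.

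Example: with q = 0.75, rA = 0.8 and rN = 0.5, s = 0.600 / (0.600 + 0.125) = 0.828. The effect is 9 × 0.828 = 7.45, against 9 × 0.75 = 6.75.

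| Non-attenders | rA | rN | True ITT | Imputed without attendance | Ratio |
|---|---|---|---|---|---|
| 15% | 80% | 50% | 7.65 | 8.11 | 1.06 |
| 15% | 80% | 30% | 7.65 | 8.44 | 1.10 |
| 25% | 80% | 50% | 6.75 | 7.45 | 1.10 |
| 25% | 80% | 30% | 6.75 | 8.00 | 1.19 |
| 35% | 80% | 50% | 5.85 | 6.73 | 1.15 |
| 35% | 80% | 30% | 5.85 | 7.49 | 1.28 |
| 25% | 80% | 80% | 6.75 | 6.75 | 1.00 |
| 25% | 60% | 80% | 6.75 | 6.23 | 0.92 |

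On a wider grid, with 10% to 50% non-attenders, the ratio runs from 1.00 to 1.60 when rA = 80% and rN falls from 80% to 20%. It runs from 0.97 down to 0.86 when rA = 60% and rN = 80%. If the effect in attenders is zero, both formulas give zero and there is no bias from this source.

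**Simulation check.** It used 316 and 217 participants, logistic multiple imputation by arm, 10 imputations, 400 runs and an assumed 70% control response. The Monte Carlo standard error is about 0.25 points. With rA = 80% and rN = 40%:

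- 75% attending: 7.8 points without attendance in the imputation and 6.8 with it (true 6.75).
- 50% attending: 6.1 without and 4.6 with (true 4.5).

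Adding attendance removes the bias to within simulation error.

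**The listed sensitivity analyses.** Complete case analysis uses responders as they are, so it carries the same responder mix. Modified ITT restricts the set to students with at least one follow-up and imputes by similar procedures. Neither brings in attendance, so agreement among the three analyses would not be evidence against this bias.

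**The case against.** **A stronger reading of the text.** A reader might infer that the outcomes of students who left the programme would be set to missing and imputed even when they completed the survey. That would matter: in the simulation it returned 9.2 points against a true 6.75 with 75% attending. The documents do not support it. The sentence is about missingness, so its bracket is most naturally a list of causes. The section opens by committing to use all observed information, the benchmark imputes only missing values, and absent or transferred students are still pursued for the survey. What remains is loose wording.

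**A stronger reading of the bias.** A reader might also infer that lost non-attenders are given the outcomes of attenders and that the effect is probably overstated. That goes too far. They are given the outcomes of the responder mix, which includes surveyed non-attenders: in the 25% example the mix is 83% to 89% attenders, against 75% in the arm. No response rate by attendance is reported, and follow-up by email, text, phone and social media was not tied to attending sessions. The direction is conditional.

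**Cohort may absorb part of it.** The pandemic group probably falls mainly in the last cohort, although that is inferred from dates. If all model variables enter the imputation, cohort does too. This has some force, but the itemised list leaves cohort out, and cohort cannot separate attenders from non-attenders within a semester.

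**Size.** With prevalences near 34.6% and 27.9% and 217 and 316 participants, the standard error of the difference is √(0.346 × 0.654 / 217 + 0.279 × 0.721 / 316) = 4.1 points before any loss. The tabulated overstatements, about 0.5 to 1.6 points, are 0.1 to 0.4 standard errors. This is fair, and it limits the urgency.

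**The missing sensitivity analysis.** Its specification could sit in an analysis plan that is not shown. However, the article points to its own section, which describes its analyses and does not include this one.

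**Conclusion.** The concern holds as a conditional weakness of the benchmark. The intervention arm is imputed as though attendance carried no information about the outcome among those lost, although attendance was tracked. The result is an overstated ITT effect if non-attenders are lost more often and the benefit depends on attendance. The article makes greater loss among non-attenders plausible but does not quantify it. With equal response or no programme effect the bias is zero, and with the reverse pattern the effect is understated.

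Under the central assumed inputs (25% non-attenders, 80% response against 30% to 50%), the excess is 0.7 to 1.25 points on a true 6.75, or 10% to 19%. That is modest beside the sampling error, but it is avoidable and the listed sensitivity analyses would not show it. The unfulfilled pointer to Sensitivity Analysis is a plain inconsistency and needs no assumption.

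**What to change.** 1. Add the number of sessions attended, or at least the tracked indicator of six or more, as an auxiliary variable in the intervention-arm imputation model for the benchmark. Separate imputation by arm makes this straightforward.
2. Keep attendance out of the outcome regression. It arises after randomisation, and adjusting for it would change the question.
3. Name cohort in the itemised imputation list, to match Statistical Analysis Models.
4. Reword the sentence on missingness so that programme attrition is not itself a type of missing data, and state that a completed survey is used as observed whatever the attendance.
5. Reconcile Handling Missing Data with Sensitivity Analysis: either describe the analysis that uses reasons for programme attrition or withdraw the pointer.

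The cost is some wording and one or two variables already held. Intervals would be slightly wider. If few non-attenders respond, the imputation would be less stable, and the six-session indicator may then be safer than the full count.
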